## Abstract

**Background:**

Patients with end-stage kidney disease (ESKD) have a high rate of mortality and specifically an increased risk of sudden cardiac death (SCD). Impaired cardiac autonomic tone is associated with elevated risk of SCD. Moreover, patients with ESKD are often vitamin D deficient, which we have shown may be linked to autonomic dysfunction in humans. To date, it is not known whether vitamin D supplementation normalizes cardiac autonomic function in the high-risk ESKD population. The VITamin D supplementation and cardiac Autonomic tone in Hemodialysis (VITAH) randomized trial will determine whether intensive vitamin D supplementation therapies improve cardiac autonomic tone to a greater extent than conventional vitamin D supplementation regimens in ESKD patients requiring chronic hemodialysis.

**Methods**/**Design:**

A total of 60 subjects with ESKD requiring thrice weekly chronic hemodialysis will be enrolled in this 2x2 crossover, blinded, randomized controlled trial. Following a 4-week washout period from any prior vitamin D therapy, subjects are randomized 1:1 to intensive versus standard vitamin D therapy for 6 weeks, followed by a 12-week washout period, and finally the remaining treatment arm for 6 weeks. Intensive vitamin D treatment includes alfacalcidiol (activated vitamin D) 0.25mcg orally with each dialysis session combined with ergocalciferol (nutritional vitamin D) 50 000 IU orally once per week and placebo the remaining two dialysis days for 6 weeks. The standard vitamin D treatment includes alfacalcidiol 0.25mcg orally combined with placebo each dialysis session per week for 6 weeks. Cardiac autonomic tone is measured via 24 h Holter monitor assessments on the first dialysis day of the week every 6 weeks throughout the study period. The primary outcome is change in the low frequency: high frequency heart rate variability (HRV) ratio during the first 12 h of the Holter recording at 6 weeks versus baseline. Secondary outcomes include additional measures of HRV. The safety of intensive versus conventional vitamin D supplementation is also assessed.

**Discussion:**

VITAH will determine whether an intensive vitamin D supplementation regimen will improve cardiac autonomic tone compared to conventional vitamin D supplementation and will assess the safety of these two supplementation regimens in ESKD patients receiving chronic hemodialysis.

**Trial registration:**

ClinicalTrials.gov, NCT01774812

## Background

More than 40,000 Canadians live with end-stage kidney disease (ESKD)—roughly 1 out of every 1,000 people, a number that has tripled over 20 years – and require life-sustaining dialysis or transplantation [1]. Patients with ESKD have a 20% annual mortality rate and an age-specific cardiovascular death rate that is 10-100x higher than the general population [2]. Sudden cardiac death (SCD) accounts for more than a quarter of deaths in the hemodialysis population, making it the leading cause of death [2]. However, as is repeatedly reflected by negative trials evaluating the effects of treatment of traditional cardiovascular disease risk factors in patients with ESKD [3-6], these deaths are not associated with typical coronary artery disease, suggesting alternative mechanisms for SCD in ESKD. As such, the pathophysiology of SCD in the ESKD population is complex and believed to require the interaction between a transient event (i.e. intermittent hemodialysis) and underlying substrate. This process induces electrical instability and ventricular arrhythmias followed by hemodynamic collapse. Two factors specific to ESKD patients that have emerged as potential contributors to this SCD-susceptible state are altered mineral metabolism, including vitamin D deficiency, and impaired cardiac autonomic tone [7-10].

### Cardiac autonomic tone

Cardiac autonomic tone is derived from beat to beat measurements of the time intervals between successive QRS intervals, specifically RR intervals. Measurement of HRV provides direct insight into abnormalities of the autonomic nervous system, which consists of the sympathetic nervous system (SNS) and the parasympathetic (vagal) nervous system (PNS) limbs [7,11,12]. HRV assesses the dynamic interaction and balance between the SNS and PNS at the level of the heart, overall providing a measure of cardiac autonomic competence [11,12]. The *a priori* main outcomes of interest are measures of the frequency domain as these parameters are direct measures of cardiac autonomic tone [11] and are most commonly described in the ESKD study population [10,13-15]. No one parameter of HRV has been established as superior in regards to their predictive ability as surrogate markers for adverse cardiovascular events [7,16-19].

Decreased HRV is associated with an increased risk of arrhythmias and cardiac death in both the general population [7] and patients with ESKD on dialysis [8,9,12-15]. Further, alterations in HRV occur more frequently in dialysis patients and corresponds with an increased risk of SCD and cardiovascular mortality [9,13]. In a study of 30 ESKD patients, 53% had autonomic dysfunction, in which 40% was isolated to the vagal (PNS) limb and 13% had combined sympathetic and vagal dysfunction [20]. Similarly, HRV findings in a study of 239 hemodialysis patients demonstrated drastic sympathetic over-activity and vagal withdrawal [15]. Another study of 383 patients with ESKD on hemodialysis found that impaired cardiac autonomic tone was independently associated with an increased risk of all-cause and cardiovascular death after adjustment for traditional cardiovascular risk factors [8]. Although HRV is a surrogate measurement, it has been established as an important and validated, non-invasive measure of cardiovascular-related mortality risk in the ESKD population [12,13,20,21]. Consequently, interventions enhancing measures of HRV, and therefore influencing cardiac autonomic control, could potentially have considerable survival benefits in the high-risk ESKD patient population.

### Vitamin D

There are multiple pharmacological analogues and formulations of vitamin D available for clinical use [22,23]. To be effective in disorders resulting from vitamin D deficiency, nutritional sources of vitamin D (cholecalciferol, vitamin D_3_; and ergocalciferol, vitamin D_2_) must undergo two enzymatic hydroxylations: 1) in the liver to 25-hydroxyvitamin D (25OHD); 2) in the kidney, 1α-hydroxylase converts 25OHD to the biologically active form of vitamin D, 1,25-dihydroxycholecalciferol (calcitriol) or 1,25- dihydroxyergocalciferol [22,23]. The liver hydroxylation is largely substrate driven, but the kidney’s 1α-hydroxylase is very tightly regulated by hormones (e.g. parathyroid hormone) and concentrations of calcium and phosphate ions [22,23]. In the VITAH trial, we use the following terminology for the specific vitamin D analogues; nutritional vitamin D therapy is provided in the form of ergocalciferol, and alfacalcidiol, is provided as the active (activated) vitamin D derivative.

In ESKD, progressive loss of functional kidney activity reduces the availability of 1α-hydroxylase within the renal tissue, which in turn reduces 1,25-dihydroxyvitamin D_3_ production [24]. ESKD patients are also commonly deficient in 25OHD due to decreased nutritional intake from intensive dietary restrictions, lack of sun exposure due to decreased mobility, and dysregulated mineral metabolism [24].

In general, vitamin D deficiency is common and associated with worse cardiovascular outcomes in both the healthy [25] and ESKD [26] populations. Furthermore, low vitamin D levels are associated with increased risk of SCD in both non-ESKD [27] and ESKD patients [28,29]. In relation to cardiovascular pathophysiology, vitamin D has been shown to influence cardiac contractility and myocardial calcium homeostasis in humans [30-33]. Furthermore, a small study of hemodialysis patients showed that treatment with activated vitamin D reduced the QT interval on electrocardiography [34]. Recently, we have not only shown that low vitamin D levels are associated with vascular physiology that increases cardiovascular risk [35], but also that poor vitamin D status is associated with an impaired ability to maintain cardiac autonomic tone in response to endogenous angiotensin II in healthy humans [36], a hormone that is chronically upregulated in the ESKD population. Furthermore, we have also demonstrated that vitamin D supplementation is associated with *normalization* of autonomic tone in response to an acute angiotensin II stressor in healthy subjects [37]. As vagal activity is markedly reduced in hemodialysis patients [15], it is possible that vitamin D supplementation could improve the cardiac autonomic response to stressors such as hemodialysis. Regardless, the impact of vitamin D therapy in the ESKD population, and on other surrogate clinical measures of cardiovascular risk has not been assessed. In an observational study, serum 25OHD predicted total and cardiovascular mortality in incident ESKD patients, but this association was abolished in patients provided therapy with calcitriol or its active analogues [26]. This novel observation suggests that intensive vitamin D therapy inclusive of 1,25-dihydroxyvitamin D_3_ analogues as well as other vitamin D derivatives may provide a more significant therapeutic and survival benefit within the severely deficient ESKD population, and thus provides the basis for assessing the therapeutic role of intensive and conventional vitamin D supplementation regimens in altering cardiac autonomic tone, as in the VITAH trial.

Evidence to date supports the safety profile of vitamin D therapy. Vitamin D deficiency is the norm in hemodialysis patients and as such, vitamin D supplementation should result in significant increase vitamin D levels. Secondly, given there is significant controversy regarding the target 25-hydroxyvitamin D level in both the general and chronic kidney disease population [38,39], we aimed to determine the effect of delivered dose of vitamin D, rather than level of vitamin D, on cardiac autonomic tone. Lastly, though there is significant practice variation, the activated and nutritional vitamin D doses chosen for the study reflect those recommended in and typically prescribed to the end-stage kidney disease population on hemodialysis [38].

Despite the high prevalence of vitamin D deficiency in ESKD, current guidelines regarding correction of vitamin D status are widely acknowledged to be opinion-based and derived from biochemical endpoints [38]. The nutritional vitamin D product (ergocalciferol) and dose proposed within this protocol is identical to that suggested by guidelines for treatment in the ESKD population [38,40]. Furthermore, treatment with other nutritional forms of vitamin D_3_ at a dose of 15,000 IU/day × 1 month [41] and 40,000 IU/day over 28 weeks, followed by 10,000 IU/day × 12 weeks [42] has been shown to be safe. A main clinical concern with activated vitamin D supplementation in the ESKD population is hypercalcemia, hyperphosphatemia and reduction in parathyroid hormone levels. This protocol employs the lowest possible dose of activated vitamin D (alfacalcidiol) available to minimize significant fluctuations in these biochemical values, though the relative importance of these changes remains unquantified within the literature [43].

In summary, the evidence to guide treatment that may minimize SCD and cardiovascular risk in ESKD is extremely limited. The VITamin D supplementation and cardiac Autonomic tone in Hemodialysis (VITAH) study is the first clinical trial to assess whether various vitamin D therapies, specifically ingestion of the combination of activated and nutritional vitamin D compared to activated vitamin D alone, influence cardiac autonomic tone and therefore cardiovascular risk in ESKD patients requiring hemodialysis.

## Methods

### Study aims

The primary aim of the VITAH trial is to determine whether 6 weeks of intensive vitamin D supplementation, consisting of alfacalcidiol 0.25mcg orally at every dialysis session combined with ergocalciferol 50,000 IU orally once per week and placebo the remaining 2 weekly dialysis sessions, will influence HRV assessment of cardiac autonomic tone, compared to 6 weeks of conventional therapy with alfacalcidiol 0.25mcg and placebo orally at every dialysis session. The secondary aim is to determine whether this intensive vitamin D supplementation influences or modulates independent activity of the sympathetic and vagal limbs of the cardiac autonomic nervous system compared to the conventional alfacalcidiol regimen.

We hypothesize that vitamin D supplementation will increase *all* cardiac autonomic parameters, but that the vitamin D treatment will specifically have the greatest impact on vagal tone. We hypothesize that cardiosympathovagal balance will decrease after vitamin D therapy due to the fact that any increase in cardiosympathetic tone will be offset by a larger increase in cardiovagal tone.

### Study design and setting

The VITAH Trial is a 2x2 cross-over, randomized-controlled trial with blinding of subjects, investigators, health care providers, as well as all study coordinators and data analysts. Hemodialysis outpatients from the Southern Alberta Renal Program will be randomized to one of two treatment sequence arms; 6 weeks of intensive vitamin D therapy (0.25 mcg alfacalcidiol at each dialysis session plus 50,000 IU of ergocalciferol once per week and placebo the remaining two weekly dialysis days), followed by a 12 week washout, and 6 weeks of conventional vitamin D therapy (0.25 mcg alfacalcidiol plus placebo at each dialysis session), or vice versa. Twenty-four hour Holter ECG monitors are applied within the first hour of the first weekly dialysis run at baseline and every 6 weeks throughout the entire 24-week duration of the trial (Figure 1). The study protocol will not impact on uremia clearance given that the dialysis prescription will remain constant. Subject recruitment began in January 2013 and will continue until 2016.

**Figure 1 F1:**
[figure not shown]
Overview of the VITAH trial.

### Ethical considerations

Ethical approval has been obtained from the Conjoint Health Research Ethics Board (Project ID: E-24846) at the University of Calgary as well as Health Canada (UC-NEPH-2012001) for all study sites involved in the trial. Two external bodies, a Data Safety Monitoring Board and a Trial Steering Committee, will monitor study progress.

### Study interventions

The intervention is the vitamin D therapy sequence, including 6 weeks of intensive therapy and 6 week of conventional vitamin D therapy, or vice versa (Figure 1). Given that the current clinical standard of care is use of activated vitamin D (one of the top drug classes prescribed as recently outlined in the United States Renal Data System [44]) in the ESKD population, a placebo arm is not included. Upon recruitment, participants who are prescribed any form of vitamin D (either nutritional or active) at that time will cease to take the medication for 4 weeks, a valid washout period employed by the PRIMO trial, a randomized controlled trial examining the effects of activated vitamin D on cardiac structure in subjects with non-dialysis dependent kidney disease [45]. Participants who are not on any form of vitamin D at the time of enrolment will be randomized to one of the two treatment sequences immediately. All participants will be randomized to Treatment Sequence 1 or Treatment Sequence 2, such that each participant will ingest both vitamin D therapy regimens in a randomized, blinded, placebo-controlled crossover design and thus act as his/her own control. A 12 week washout period was chosen between each 6 week vitamin D treatment block to ensure that there are no carryover effects from either study period as the t_1/2_ for alfacalcidiol is approximately 4 hours, and the t_1/2_ for ergocalciferol is 19–48 hours [22,23,46].

### Identification of eligible subjects

Eligible subjects are stable, thrice weekly hemodialysis outpatients within the Southern Alberta Renal Program in Calgary, Alberta. Inclusion and exclusion criteria are outlined in Table 1. All patients in the Southern Alberta Renal Program hemodialysis units will be reviewed. Individuals who meet inclusion criteria will be identified by nephrologists or study investigators. After clearance from the individual’s primary nephrologist, the name will be forwarded to the study coordinators and recorded in recruitment logs. Informed written consent will be obtained from the participant, power of attorney or legal substitute decision-maker. Once eligibility is confirmed by reviewing the chart or from participant interview, baseline clinical (i.e. ESKD etiology, comorbidities, cardiovascular history, dialysis prescription and adequacy details), demographic and medication data will be obtained. Subjects will be randomized 1:1 to one of the two treatment sequences.

**Table 1 T1:** VITAH trial inclusion and exclusion criteria

**Inclusion criteria**	**Exclusion criteria**
• Age ≥ 18 years	• Any major cardiovascular event within the last 6 months prior to enrolment (this includes, but is not limited to, new onset arrhythmia, hospitalization for a cardiovascular complication)
• Thrice weekly hemodialysis outpatient within the Southern Alberta Renal Program	
• Physician consent to participate	• Refusal to cease vitamin D therapy for four (4) weeks prior to initiation of the study
• Ability and agreement to cease any prior vitamin D medication for four (4) weeks prior to initiation of the study	• Palliative status or metastatic malignancy
• Ability to comprehend study protocol and provide oral and written consent in English (native language or translated)	• Known or anticipated upcoming change in dialysis modality including transfer to peritoneal dialysis, kidney transplant, or change in current hemodialysis schedule/duration

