### Data collection

Ambulatory electrocardiography (Holter) data is recorded for 18–24 hours using a standard bipolar 3-lead configuration (GE Healthcare, SEER MC; Milwaukee, USA). HRV is analyzed using a commercial Holter analysis system (MARS v. 7; GE Healthcare; Milwaukee, USA). Power spectral density analysis, which transforms the electrocardiographic signals into measures of frequency domain HRV (representing activity of the cardiac autonomic nervous system) are calculated. Autonomic activity is categorized into spectral bands: total power (TP), very-low frequency (VLF, 0.003-0.04 Hz), low-frequency (LF, 0.04-0.15 Hz) and high-frequency (HF, 0.15-0.4 Hz) domains [7,8,17-19]. Absolute LF and HF parameters are then squared and log-transformed (*ln* ms [2]) and converted to normalized units (nu). Overall cardiosympathovagal balance (LF:HF) is derived from these measures. Time domain HRV measurements are also calculated (Table 2) [7,8,17-19].

**Table 2 T2:** Description of heart rate variability data to be analyzed from 24- hour Holter recording

**Heart rate variability parameter (Acronym)**	**Description/Physiological representation**
**Low frequency (LF)**	Represents contribution of baroreflex activity in overall cardiovascular control
**High frequency (HF)**	Represents contribution of cardiac parasympathetic/vagal nervous activity
**Low to high frequency ratio (LF:HF)**	Represents the interplay between sympathetic and parasympathetic limbs of the autonomic nervous system

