### Primary outcome

The primary outcome of the study is sympathovagal balance (LF:HF), interpreted as the overall balance on stimulatory and inhibitory cardiac autonomic control, from baseline to the final study day within each 6 week treatment block (0 and 6 weeks, 18 and 24 weeks). Comparison of measured sympathovagal balance throughout each of the vitamin D supplementation treatment blocks as well as the 12-week washout period will allow for statistical interpretation of whether presence or absence of oral vitamin D therapy alters cardiac autonomic function within this population. An improvement in sympathovagal balance can be interpreted by a downward shift in LF:HF, in which a smaller value indicates greater contribution of cardioprotective vagal activity (Table 2).

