### Study withdrawal

Given that the primary and secondary outcomes require the measurement of cardiac autonomic tone with a Holter monitor, follow up for these outcomes can only occur if the subject is alive and accessible for monitoring. Therefore, subjects will be censored and withdrawn from follow-up under the following circumstances; subject or primary nephrologist request, transfer to peritoneal dialysis, kidney transplantation, transfer of subject to a non-study hemodialysis unit, hospitalization, or death. Upon withdrawal from the study, any data collected up to that time will be utilized in a last observation carried forward (LOCF) approach.

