### Sample size calculation

While we are not aware of any studies examining the use of vitamin D on the primary outcome of this study, previous work by Kontopoulous et al. [47] has demonstrated that post-myocardial infarction (MI) patients (n = 25) randomized to receive 5–10 mg of quinapril (angiotensin converting enzyme inhibitor) per day for 35 days immediately following an MI displayed a 46% reduction in LF:HF from baseline to 6 weeks (mean ± SE: 10 ± 0.7; 5 ± 0.5), while those randomized (n = 25) to receive 50–100 mg of metoprolol per day for 35 days following an MI displayed a similar 36% reduction in LF:HF from baseline to 6 weeks (mean ± SE: 9 ± 0.6; 6 ± 0.4). As such, given that 1) vitamin D deficiency is the norm in hemodialysis patients, 2) vitamin D downregulates the renin-angiotensin system [24,25,35], and 3) increased RAS activity is associated with alterations in cardiac autonomic tone [35-37], we feel there is sufficient justification for the sample size calculation herein**.** Based on these observations, we estimate the standard deviation of the pooled difference in LF:HF from both treatment sequences as 4.53. Using a 2 × 2 crossover design (2 sequences or treatment orderings and 2 time periods or occasions) and anticipating a 20% or larger reduction in LF:HF observed after 6 weeks of treatment with combined vitamin D vs. the reduction observed after 6 weeks of treatment with alfacalcidiol alone, we estimate that 54 subjects will be required (α = 0.05, β = 0.9). In anticipation of a 10% dropout rate, approximately 60 subjects in total will be recruited.

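### Table 1 admits patients with established atrial fibrillation or flutter, or with a ventricular-paced rhythm, in whom the RR-based primary outcome does not reflect autonomic tone

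*Protocol article*

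**What the plan says.** Under Identification of eligible subjects, the population is given as follows: "Eligible subjects are stable, thrice weekly hemodialysis outpatients within the Southern Alberta Renal Program in Calgary, Alberta". Table 1 then lists the criteria. The one item that touches heart rhythm excludes "Any major cardiovascular event within the last 6 months prior to enrolment (this includes, but is not limited to, new onset arrhythmia" and cardiovascular hospitalization in the same window. No criterion mentions sinus rhythm, chronic arrhythmia or a pacemaker.

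The Background section on cardiac autonomic tone states the measurement basis: "Cardiac autonomic tone is derived from beat to beat measurements of the time intervals between successive QRS intervals, specifically RR intervals". Data collection defines the bands as "low-frequency (LF, 0.04-0.15 Hz) and high-frequency (HF, 0.15-0.4 Hz) domains". The Primary outcome section fixes the favourable direction: "An improvement in sympathovagal balance can be interpreted by a downward shift in LF:HF". The secondary outcomes add LF, HF, SDNN, SDANN and pNN50, which are all RR-based, and blood measurements, which are not.

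**The concern.** LF:HF is informative about autonomic balance only when the sinus node sets the beat-to-beat interval. In established atrial fibrillation the ventricular intervals are largely irregular for other reasons, and in a ventricular-paced rhythm the device sets them. The article does not spell out this physiological premise, but it is implicit in its own account of what RR intervals are meant to show.

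The open-ended wording of the Table 1 item (the list of examples is not exhaustive) widens the set of recent events. It does not reach a condition that has been present for years. The word stable in the population statement does not exclude such a patient either; permanent fibrillation or long-standing pacing is compatible with being stable.

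At stake are randomized places in a small crossover trial. A subject of this kind either contributes a number that cannot respond to treatment or has no usable primary outcome in either period. A second, less certain risk is that a change of rhythm between the start and end of a block is taken for a treatment response.

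**Working it through.** **Inputs.** From Sample size calculation: "we estimate the standard deviation of the pooled difference in LF:HF from both treatment sequences as 4.53"; alpha 0.05; a figure of 0.9 printed as beta and read here as power; a 20% reduction; 54 subjects, 60 after 10% dropout; planning values of LF:HF falling from 10 to 5 and from 9 to 6, both in post-infarction patients. From Data collection: the LF and HF band limits. Assumed, because the documents give none: the share f of enrolled subjects with an uninformative rhythm (5%, 10%, 20%) and the LF:HF level in hemodialysis patients.

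**Step 1. Reproduce the plan's figure.** The absolute difference is not stated; 20% of 10 gives 2.0. With a two-sided alpha:

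n = (SD × (1.960 + 1.282) / difference)² = (4.53 × 3.242 / 2.0)² = 53.9, so 54. Then 54 / 0.90 = 60.

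The stated numbers reproduce. The paired-t power at n = 54 is 0.89.

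**Step 2. Dilution if uninformative subjects stay in the analysis.** The expected difference becomes 2.0 × (1 − f). Two assumptions about the SD bracket the result:

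- (a) These subjects have zero difference and no variance, so SD = √[(1 − f) × 4.53² + f(1 − f) × 2.0²].
- (b) The SD stays at 4.53.

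| f (assumed) | Expected difference | SD under (a) | Power (a) | Power (b) |
|---|---|---|---|---|
| 0 | 2.0 | 4.53 | 0.89 | 0.89 |
| 5% | 1.9 | 4.44 | 0.87 | 0.86 |
| 10% | 1.8 | 4.34 | 0.85 | 0.82 |
| 20% | 1.6 | 4.13 | 0.80 | 0.72 |

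**Step 3. Loss if their recordings are rejected instead.** The difference stays at 2.0 and n falls to 54 × (1 − f) = 51.3, 48.6 or 43.2. With 51, 49 and 43 subjects, paired-t power is 0.87, 0.86 and 0.81. Rejecting recordings softens the loss but does not recover the randomized places.

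**Step 4. A rhythm change read as improvement.** This step rests on the assumption that an irregular rhythm gives a roughly flat RR spectrum. From the stated bands, LF:HF = (0.15 − 0.04) / (0.40 − 0.15) = 0.11 / 0.25 = 0.44. Simulating independent RR intervals gives 0.42 to 0.72, depending on mean rate and resampling method. One change from sinus rhythm to this level at the end of one block shifts the mean difference over 54 subjects by (start − 0.44) / 54:

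| Sinus starting value | Fall | Shift in mean of 54 |
|---|---|---|
| 10 (post-infarction planning value) | 9.56 | 0.18 |
| 9 (post-infarction planning value) | 8.56 | 0.16 |
| 3 (assumed) | 2.56 | 0.05 |
| 1 (assumed) | 0.56 | 0.01 |

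As a percentage, the fall exceeds the planned 20% for any start above 0.44 / 0.8 = 0.55, or above 0.72 / 0.8 = 0.90 at the upper simulated level. The direction is therefore clear over most of the range, but the absolute size is not.

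**The case against.** The strongest reply concerns how far the point reaches, and much of it stands.

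- **Recording rules.** Rules for editing or rejecting Holter segments commonly sit in the full protocol or analysis plan. Their absence from an article is no finding, and the time-domain measures are already defined on normal beats. This is accepted. The printed eligibility list is a different matter: Step 3 shows that rejecting recordings still leaves a loss.
- **Fibrillation counted as benefit.** A reader might infer that a lapse into fibrillation on treatment would be scored as a large improvement. The documents do not support this as a certainty. They do not say what LF:HF does in fibrillation, and the baselines of 9 and 10 are not from hemodialysis patients. The lapse must also coincide with a block-end recording. If it leads to admission, Study withdrawal applies instead: the listed reasons include "transfer of subject to a non-study hemodialysis unit, hospitalization, or death", after which "any data collected up to that time will be utilized in a last observation carried forward (LOCF) approach".
- **Bias in the test.** The primary test is described as non-parametric. If it is a signed-rank test, an extreme value counts only through its rank. Simulating 54 differences with SD 4.53, no true effect and a fall of 9.56 leaves the error rate at about 0.05 with one lapse. It reaches about 0.08 with three lapses all in the same treatment. Lapses unrelated to treatment can go either way; with three in random directions the error stays near 0.05 and power is about 0.81. That is noise, not bias.
- **Scope.** A reader might also infer that every outcome is affected. The blood measurements and safety are not RR-based.
- **Size.** No prevalence is given. At 5% to 10% the power loss is modest, and 20% is an assumption.

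None of this closes the gap in Table 1.

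**Conclusion.** The eligibility point holds. As printed, Table 1 allows enrolment of patients whose primary outcome, and all of whose heart rate variability outcomes, cannot be interpreted as autonomic tone. Nothing else in the article prevents it.

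The routine consequence is reduced sensitivity: from paired-t power of 0.89 to about 0.86-0.87, 0.82-0.85 or 0.72-0.80 if 5%, 10% or 20% of subjects cannot respond. These figures rest on a difference of 2.0, the stated SD of 4.53 and assumed shares. Misreading a rhythm change as improvement is possible, because the Primary outcome section treats a fall in LF:HF as favourable, but it is secondary. Its size depends on an assumed flat spectrum (LF:HF about 0.4 to 0.7) and on an unknown hemodialysis baseline. The sample size figure itself is not wrong on this account.

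**What to change.** Add one criterion to Table 1 requiring sinus, non-paced rhythm, thereby excluding established (permanent or persistent) atrial fibrillation or flutter and ventricular pacing. Verify it from the chart and cardiovascular history, which are already reviewed at screening, before randomization. Do not make exclusion depend on the baseline Holter. The recorder is applied during the first weekly dialysis run, while study drug is given at the start of the session and randomization follows consent. A Holter-based exclusion would therefore need an extra screening recording or would remove subjects after randomization.

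For subjects already randomized, state that a recording judged predominantly non-sinus or paced, by a reader blind to treatment, is not evaluable for LF:HF. Report a new arrhythmia under safety, not as a change in LF:HF.

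The cost is a short amendment and no new procedure. Some patients become ineligible (how many is unknown), recruitment is slightly slower, and the result applies to hemodialysis patients in sinus rhythm. A chart check will miss some undocumented arrhythmia; the blinded reading rule covers that remainder.
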